### Ethics and trial registration

All participants will be completely informed about the study and will be asked to sign an informed consent form. The study protocol has been approved by the Institutional Review Boards (IRBs) of all participating institutions. This clinical trial was registered with the Clinical Research Information Service (CRIS registration No. KCT0003523, https://cris.nih.go.kr/cris/search/detailSearch.do/13022).

### Sample size calculation

Based on previously published studies, we hypothesized that the rate of AL would be 15% and 5% in the HL and LL groups, respectively. With a two-sided *α* of 0.05 and a power of 0.8, the sample size was calculated as 314 patients (157 per group), considering an estimated dropout rate of 10%. The formula used to calculate the sample size is as follows:$$n=\frac{{\left({z}_{\alpha }+{z}_{\beta /2}\right)}^2}{{\left(\delta -|\varepsilon |\right)}^2}\left[\frac{p_1\left(1-{p}_1\right)}{k}+{p}_2\left(1-{p}_2\right)\right]$$

(*α* = alpha; *β* = 1 − power; *ε* = *p*_1_ − *p*_2_; *δ* = noninferiority margin; *n*_1_ = *kn*_2_)

### Randomization

Random allocation will be performed in a 1:1 ratio using the permuted block technique, stratified by gender and preoperative chemoradiotherapy. The randomization sequence will be generated independently by the study statistician before being provided to the randomization contact for onward use. After enrolling patients, the investigators will contact the research coordinator of the initiating institution (School of Medicine, Kyungpook National University) via telephone on the day before the surgery, and they will be able to know which group the registered patient is assigned to.

### Blinding

Due to the nature of the study, the patients will be blinded, but the surgeons will not be blinded. Likewise, the outcome assessors will not be blinded because the surgeon in charge will be the assessor of the primary outcome (symptomatic AL). However, the data analysts will be blinded.

### Assessment of outcomes

The primary outcome is the incidence of AL, and the secondary outcomes are quality of life; urinary, sexual, and defecatory functions; and 3-year disease-free survival. After enrolment, patients will undergo preoperative evaluations, including medical history, physical examination, digital rectal examination, laboratory tests, colonoscopy, and radiologic tests. All patients will complete the questionnaires before and at 6, 12, 24, and 36 months after the surgery (Fig. 2). Patients with a diverting stoma will answer a questionnaire on defecatory function after stoma reversal surgery. The questionnaires will include the European Organization for Research and Treatment of Cancer QLQ-C30 for quality of life, the International Prostate Symptoms Score for urinary function, the Female Sexual Function Index, the International Index of Erectile Function-5 for sexual function and retrograde ejaculation, and the Low Anterior Resection Syndrome score for defecatory functions, which are all validated and widely used [23–28].

**Fig. 2 Fig2:**
[figure not shown]
Schedule of enrolment, interventions, and assessments

Investigators will check and record AL within 1 month after surgery (Fig. 2). AL is defined as a defect of the intestinal wall at the anastomotic site resulting in peritonitis, rectovaginal fistula, or pelvic abscess [29], which is confirmed by physical examination, rigid rectoscopy, or abdominopelvic computed tomography (CT). We will include symptomatic AL (grades B and C) in the primary endpoint analysis [29].

All patients will be followed up at 6-month intervals for 3 years. Serum carcinoembryonic antigen tests and abdominopelvic and chest CT will be conducted semiannually, and colonoscopy will be performed annually. Recurrence will be diagnosed via radiological detection of lesions or histological confirmation. A detailed schedule of the assessments is shown in Fig. 2.

### Statistical analysis

We will analyse the data using two analysis sets: the intention-to-treat set, considering all patients as randomized regardless of whether they underwent the randomized surgical intervention, and the per-protocol set. Considering that there will be very few patients expected to crossover, these analyses should be very closely matched. Because symptomatic AL will be evaluated during hospitalization after surgery, we expect no missing data on the primary outcome. For other missing data, we will utilize multiple imputation under the assumption of missing at random.

Categorical variables will be compared using the *χ*^2^ or Fisher’s exact test, and continuous variables will be compared using Student’s *t*-test or the Mann–Whitney *U*-test. Disease-free survival will be measured from the date of surgery to the date of recurrence or death. Survival rates will be estimated and compared using the Kaplan–Meier method and log-rank test, and the Cox proportional hazard model will be utilized for multivariable survival analysis. Subgroup analyses will be conducted for each randomization stratum. All variables with a *p*-value < 0.05 will be considered significant. All statistical analyses will be performed using SPSS 27.0 (IBM Inc., Armonk, NY, USA).

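### The stated tests for anastomotic leak and disease-free survival leave out the two randomisation factors, and the primary test is left open between chi-square and Fisher; the cost is small and removable by wording alone.

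*Protocol article*

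**What the plan says.** Under Randomization, the protocol article allocates 1:1 by permuted blocks, "stratified by gender and preoperative chemoradiotherapy", which gives four strata.

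Under Statistical analysis, "Categorical variables will be compared using the" chi-square or Fisher's exact test. AL, the primary outcome, is categorical, so this sentence is the only stated test for it. No rule for choosing between the two tests is given. Disease-free survival is compared by the log-rank test, with a multivariable Cox model whose covariates are not listed. The strata are mentioned once: "Subgroup analyses will be conducted for each randomization stratum".

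The Sample size calculation section gives the assumed rates: "we hypothesized that the rate of AL would be 15% and 5% in the HL and LL groups, respectively". The design error rates are 5% (two-sided) for type I and 20% for type II. The resulting target is "314 patients (157 per group), considering an estimated dropout rate of 10" per cent. The Statistical analysis section defines the intention-to-treat set as all patients as randomised and expects no missing data on the primary outcome.

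**The concern.** Stratified randomisation balances the arms on gender and chemoradiotherapy. When those factors predict the outcome, balance reduces the true variance of the between-arm difference. A test that ignores the factors still uses the larger variance of an unstratified comparison. Its standard error is then too wide, its real type I error falls below 5%, and some power is given away.

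The second issue is separate. Chi-square and Fisher do not reject on the same set of tables. If the protocol does not say which one decides the primary endpoint, the verdict in a borderline result depends on a choice that can be made once the counts are known. Blinding the analysts to arm labels does not prevent this, because the 2×2 counts alone show which test falls below 0.05. The stated power also belongs to only one of the two tests.

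**Working it through.** **Inputs from the protocol article.** AL rates 15% (high ligation) and 5% (low ligation); two-sided alpha 0.05; power 0.80; 157 per arm including 10% dropout; four strata.

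**Assumptions, not in the document.** 60% men, 30% with chemoradiotherapy, and odds ratios for AL of 1 to 3 for each factor.

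**1. Reproduce the planned size.** The pooled-variance, uncorrected chi-square formula is

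n = [z(0.975)·√(2p̄(1−p̄)) + z(0.80)·√(p₁(1−p₁) + p₂(1−p₂))]² / (p₁−p₂)², with p̄ = 0.10.

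n = [1.960·√0.18 + 0.842·√0.175]² / 0.10² = 140.1, so 141 per arm. Then 141 / 0.90 = 156.7, so 157 per arm and 314 in total, an exact match. Alternatives do not match: unpooled variance gives 138, then 154; continuity correction gives 160, then 178; the printed formula taken literally with a zero margin gives 150, then 167. The plan is numerically an uncorrected chi-square design.

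**2. Exact power and size of the two named tests**, by full enumeration of both binomials:

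| Per arm | Test | Power, 15% vs 5% | Size, 10% in both arms |
|---|---|---|---|
| 141 | chi-square | 81.7% | 4.9% |
| 141 | Fisher | 76.5% | 3.2% |
| 157 | chi-square | 86.1% | 5.1% |
| 157 | Fisher | 81.6% | 3.2% |

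Fisher first reaches 80% at 151 evaluable per arm (80.06%; 79.7% at 150).

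**3. How often the choice of test decides the result.** At both sample sizes, no table is significant by Fisher but not by chi-square. The disagreement rate is therefore the difference in power: 81.7 − 76.5 = 5.2% of trials at 141 per arm, and 86.1 − 81.6 = 4.6% (unrounded 4.56) at 157. Under a common 10% rate it is 1.7% and 1.8%. Two examples at 157 per arm: 19 versus 9 leaks gives chi-square p = 0.048 and Fisher p = 0.073; 21 versus 10 gives 0.037 and 0.057. The design expects 157 × 0.15 ≈ 24 versus 157 × 0.05 ≈ 8.

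**4. Effect of ignoring the strata.** Simulation at 141 per arm, 200,000 trials per scenario, exact balance within strata. Marginal AL rates are 15% versus 5% for power and 10% in both arms for size.

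| Odds ratios (gender / chemoradiotherapy) | Size, chi-square | Size, CMH | Power, chi-square | Power, CMH |
|---|---|---|---|---|
| 1 / 1 | 4.9% | 5.0% | 81.6% | 81.8% |
| 2 / 2 | 4.6% | 4.9% | 81.8% | 82.5% |
| 3 / 2 | 4.5% | 4.9% | 81.8% | 82.9% |
| 3 / 3 | 4.3% | 5.0% | 82.2% | 83.7% |

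The power given up is 0.7 points at 2/2 and 1.5 points at 3/3. At 1/1 the difference is about 0.2 points.

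**5. Is Fisher needed?** At 141 per arm and a 10% common rate, 141 × 0.10 ≈ 14 leaks per arm are expected. An expected cell below 5 requires fewer than 10 leaks in total. That has probability of about 1 in 100,000, both at 15% versus 5% and at 10% versus 10%.

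No magnitude was computed for the log-rank test. The argument there is the same in direction only.

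**The case against.** The case against has four parts.

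*An unadjusted test is valid.* This stands. The error is conservative, so type I error is controlled, and the power loss is at most about 1.5 points under assumptions the document does not supply. It limits the size of the point but does not remove it, because a better-matched analysis costs nothing.

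*Chi-square or Fisher is shorthand.* The usual reading is chi-square unless expected counts are small, and the sample size was built for chi-square. Under that convention Fisher would almost never be used for AL. This is plausible, but the convention is not written down, so the choice remains formally open.

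*The article condenses a fuller protocol.* Covariate lists and test-selection rules are often left to that document, and their absence is not held against the article. The point rests on what the article does state: it names the tests, and it gives the strata a role only as subgroups. The Cox model could include the two factors, but its covariates are not stated and it concerns survival, not AL.

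*The power claim.* A reader might infer that the trial misses its stated 80% power if Fisher is used. The document does not support this as a general statement. The 76.5% applies at 141 per arm, after the planned 10% loss. The article's own intention-to-treat set, with no missing AL expected, has 157 per arm, where Fisher gives 81.6%. The shortfall arises only below about 151 evaluable per arm, for instance in the per-protocol set or if patients whose participation is discontinued because of the operation performed are not counted. It would also be wrong to attribute it to the omitted strata: it comes from the conservatism of the exact test.

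**Conclusion.** The point holds as an improvement in method with a small, quantified gain; it is not an error that threatens the trial. The stated tests do not use the stratification factors. If gender and chemoradiotherapy each carry an odds ratio of 2 to 3 for AL, the unadjusted chi-square runs at about 4.3% to 4.6% instead of 5% and gives up about 0.7 to 1.5 points of power at 141 per arm. If they are not prognostic, nothing material is lost. Chi-square stays above 80% in every scenario examined. These figures rest on assumed prevalences and odds ratios.

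The open choice of test has the larger practical effect: about 1 trial in 20 under the design alternative would be declared significant by chi-square and not by Fisher. That figure needs no assumption beyond the article's own rates and sample size. Whether Fisher would meet 80% power depends on how many patients are analysed, and the article points both ways: the sample size allows for 10% loss, while the analysis section expects none for AL.

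**What to change.** Name one primary analysis of AL: a Cochran-Mantel-Haenszel test stratified by gender and preoperative chemoradiotherapy, reported with a stratum-weighted risk difference and its 95% CI. Keep the uncorrected chi-square as a sensitivity analysis, and state that Fisher's exact test is not used for the primary table. Use the same two factors in a stratified log-rank test and Cox model for disease-free survival. State which analysis set the 80% power refers to.

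The cost is wording in the protocol or analysis plan. Sample size, data collection and patient care are unaffected. The article reports that the trial was still enrolling, so the change could be fixed before the outcome data are analysed.

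### Quality-of-life and functional scores have a preoperative value and four follow-ups, but the only stated comparison is an unadjusted two-sample test; adjusting for baseline would gain precision at no cost

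*Protocol article*

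**What the plan says.** The Assessment of outcomes section of the Protocol article states that "the secondary outcomes are quality of life; urinary, sexual, and defecatory functions; and 3-year disease-free survival". On timing it says "All patients will complete the questionnaires before and at 6, 12, 24, and 36 months after the surgery". The instruments are the QLQ-C30, the International Prostate Symptoms Score, the Female Sexual Function Index, the IIEF-5 and the Low Anterior Resection Syndrome (LARS) score. There is one exception to the schedule: "Patients with a diverting stoma will answer a questionnaire on defecatory function after stoma reversal surgery".

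The Statistical analysis section gives one general rule for measurements of this kind: "continuous variables will be compared using" Student's t-test or the Mann-Whitney U-test. The only regression model named is for survival: "the Cox proportional hazard model will be utilized for multivariable survival analysis". For incomplete data on anything but the primary outcome it says "For other missing data, we will utilize multiple imputation under the assumption of missing at random".

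No sentence mentions the preoperative score as a covariate, a change score, a repeated-measures model or a main time point for the questionnaires.

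**The concern.** The design collects five measurements per scale, and the first is taken before the operation. A preoperative score usually predicts the later score in the same patient. A two-sample test on a follow-up score leaves that predictable part in the error term, and it leaves any chance difference between the arms at baseline in the estimated effect.

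This matters because the Background section gives functional outcome as one of the main reasons to compare the two ligation levels, while the sample size was set for leak alone. The functional comparisons therefore have whatever precision the leak calculation happens to leave them. The two sexual-function indices have less, since each is answered by one sex and so uses only part of the sample. Information already collected should not be left unused there.

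**Working it through.** **1. The plan's own figure.** The sample size section states that "we hypothesized that the rate of AL would be 15% and 5% in the HL and LL groups, respectively", with two-sided α 0.05, power 0.80 and 10% dropout. With pooled variance under the null (mean rate 0.10):

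n per arm = [1.960·√(2·0.10·0.90) + 0.842·√(0.15·0.85 + 0.05·0.95)]² / 0.10² ≈ 140.1, rounded up to 141.

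141 / 0.90 = 156.7, rounded up to 157 per arm, or 314 in total. The figure is reproduced. It concerns leak only, and nothing below changes it.

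**2. Inputs for the scores.** The documents give no standard deviation, correlation, target difference, sex split or completion rate for any scale. I assume SD = 1, equal variance before and after surgery, and a baseline-to-follow-up correlation r of 0.4 to 0.6, with 0.3 and 0.7 as outer limits.

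**3. Variance of the arm difference at one visit, relative to a t-test on the follow-up score.**
- t-test on follow-up: 1
- t-test on change from baseline: 2(1 − r)
- ANCOVA on baseline: 1 − r²

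| r | t-test, follow-up | t-test, change | ANCOVA | Equivalent sample, 1/(1 − r²) |
|---|---|---|---|---|
| 0.3 | 1.00 | 1.40 | 0.91 | 1.10 |
| 0.4 | 1.00 | 1.20 | 0.84 | 1.19 |
| 0.5 | 1.00 | 1.00 | 0.75 | 1.33 |
| 0.6 | 1.00 | 0.80 | 0.64 | 1.56 |
| 0.7 | 1.00 | 0.60 | 0.51 | 1.96 |

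For r between 0.4 and 0.6, ANCOVA removes 16% to 36% of the variance, equal to 19% to 56% more patients. A change score never beats it, because 2(1 − r) − (1 − r²) = (1 − r)² ≥ 0.

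**4. In terms of detectable difference.** Take 141 evaluable patients per arm, which suits a scale answered by both sexes. The t-test has 80% power for (1.960 + 0.842)·√(2/141) = 0.334 SD. Multiplying by √(1 − r²), ANCOVA detects 0.318, 0.289 and 0.238 SD at r = 0.3, 0.5 and 0.7. At a true difference of 0.334 SD its power is 83.6%, 89.9% and 97.5%.

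**5. Using the visits together.** If any two visits correlate at ρ, the baseline-adjusted mean of the four follow-ups has relative variance (1 + 3ρ)/4 − ρ². This is 0.385, 0.375 and 0.285 at ρ = 0.3, 0.5 and 0.7. It answers a different question (the average effect over three years), so it shows what a joint analysis offers and does not measure a loss on the single-visit contrast.

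**The case against.** **The sentence is generic, and this is a condensed article.** The rule for continuous variables names no questionnaire and may also be meant for baseline or perioperative data. The full protocol and any analysis plan are not shown, and covariates and model form are often left to them. This limits how much can be read into the text. It does not remove the point: the article does state a method, it is the only one that could apply to a continuous score, and a better one is available for data already being collected.

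**Stronger readings that the text does not support.**
- A reader might infer that the baseline score is discarded. That is not established, because a t-test on change from baseline fits the wording. Such a test is not stated either, and step 3 shows that it is no better than ANCOVA.
- A reader might infer a separate test at each visit, each judged by the rule that a p-"value < 0.05 will be considered significant". Four independent tests would carry a 1 − 0.95⁴ = 18.5% chance of at least one false positive per scale, and about 13% to 17% by simulation with correlations of 0.7 to 0.3. The article does not say that every visit will be tested, so I do not count this.
- A reader might infer that patients with partial follow-up drop out of the comparison. The planned multiple imputation says otherwise.
- A reader might infer bias. An unadjusted comparison of randomized arms is valid.

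**Limits on size.** The gain rests wholly on an assumed correlation and applies to ANCOVA against a t-test. It does not transfer directly to the Mann-Whitney test, or to scores analysed as categories under the χ² or Fisher rule. All of this stands.

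**Conclusion.** The point holds as one of efficiency. For secondary scores with a preoperative value and four scheduled follow-ups, the only stated comparison is an unadjusted two-sample test. It gives up precision and leaves chance baseline imbalance in the estimate. At one visit the loss is 16% to 36% of the variance for an assumed correlation of 0.4 to 0.6, and 9% to 49% over the wider range of 0.3 to 0.7.

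The LARS score does not share the full schedule, because early values will be absent by design in patients whose stoma has not been reversed. The primary leak analysis and the sample size are unaffected. This should be changed, but the trial's main conclusion does not depend on it.

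**What to change.** For the quality-of-life, urinary and sexual-function scores, replace the two-sample test with a baseline-adjusted analysis. There are two suitable forms:
- a mixed model for repeated measures with arm, visit, arm-by-visit, preoperative score and the randomization stratification factors (gender and preoperative chemoradiotherapy), omitting sex for the sex-specific scales; or
- ANCOVA at one named time point with the same covariates.

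Report the adjusted mean difference with its 95% confidence interval. In the mixed model, naming one visit as the main contrast also settles which result is to be quoted. The t-test or Mann-Whitney test can remain for description.

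Analyse the LARS score separately, or at a time point after stoma reversal, and say how patients not yet reversed are handled. Their early values are not ordinary missing data.

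The cost is wording only. No extra data are needed, SPSS can fit either model, and the article reports the trial as still enrolling, so the change can be fixed before the data are analysed.

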## Methods/design

### Study design

This multicentre, prospective, randomized clinical trial will be conducted in nine tertiary hospitals in Korea. It is a superiority trial involving two parallel groups with a 1:1 allocation ratio. The study protocol is written per the Standard Protocol Items: Recommendations for Interventional Trials (SPIRIT) checklist [21].

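### One p < 0.05 rule covers the primary test, the secondary outcomes and the stratum subgroups alike, so isolated secondary or single-stratum results would be called significant too easily

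*Protocol article*

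**What the plan says.** The article names one primary outcome, the incidence of AL. Under Assessment of outcomes, "the secondary outcomes are quality of life; urinary, sexual, and defecatory functions; and 3-year disease-free survival". Five questionnaires (QLQ-C30, IPSS, FSFI, IIEF-5 and the LARS score) are completed before surgery and at 6, 12, 24 and 36 months.

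The Sample size calculation attaches the error rate to AL alone: "With a two-sided *α* of 0.05 and a power of 0.8", for AL rates of 15% and 5%.

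The Statistical analysis section lists two-group tests for categorical and continuous variables, and Kaplan–Meier, log-rank and Cox methods for disease-free survival (DFS). It then states: "Subgroup analyses will be conducted for each randomization stratum". The next sentence is the decision rule: all variables with a p-value "< 0.05 will be considered significant". Under Randomization, the strata are formed by gender and preoperative chemoradiotherapy. The article gives no order of testing, no principal time point and no exploratory label for secondary or subgroup results.

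**The concern.** The sentence is a stated decision rule that exempts nothing, so this is more than detail left to another document. Two consequences follow if it is applied as written.

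First, a chance difference in one functional score at one visit would be called significant in the same terms as a difference in AL, including when AL shows nothing. The functional domains are formal secondary objectives, and the Abstract hopes the trial will help standardize rectal cancer surgery, so such a result could carry weight.

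Second, the rule follows directly on the per-stratum subgroup analyses. A reader applying it would label each stratum significant or not and compare the labels. That comparison does not test whether the effect differs between strata.

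**Working it through.** **1. The plan's own figure.** Inputs from Sample size calculation: 15% v 5%, two-sided 0.05, power 0.80, dropout 10%. With pooled variance under the null and no continuity correction:

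n = [1.960 × √(2 × 0.10 × 0.90) + 0.842 × √(0.15 × 0.85 + 0.05 × 0.95)]² / 0.10² = 140.1, rounded up to 141 per arm.

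141 / 0.90 = 156.7, rounded up to 157 per arm, 314 in total. The stated size is reproduced. It supports one test, on AL, at 5%.

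**2. Secondary results, no true differences.** The chance of at least one p < 0.05 among m independent tests is 1 − 0.95^m. The number of tests is an assumption, because the article does not state it.

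- Five domains, one test each: 1 − 0.95^5 = 0.226.
- Five questionnaires × four postoperative visits + DFS = 21 tests: 1 − 0.95^21 = 0.659, with 21 × 0.05 = 1.05 false positives expected.

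Tests on the same questionnaire at successive visits are correlated. Simulating the 21 tests as correlated z statistics, with FSFI and IIEF-5 treated as sex-specific, gives:

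| Correlation between visits | Correlation between instruments | Chance of at least one false positive |
|---|---|---|
| 0 | 0 | 0.66 |
| 0.5 | 0.2 | 0.58 |
| 0.7 | 0.3 | 0.50 |
| 0.9 | 0.4 | 0.39 |

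The range is therefore about 0.4 to 0.66.

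**3. Subgroups, identical true effect.** Take 141 evaluable patients per arm and a two-level factor, with true AL rates of 15% and 5% in both levels, so that there is no interaction on any scale. The article gives no expected sizes for the levels, so the splits are assumed. P1 and P2 are the exact binomial powers in the two levels. The chance that exactly one level reaches p < 0.05 is P1(1 − P2) + P2(1 − P1).

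| Split (per arm) | Test | P1 | P2 | Exactly one |
|---|---|---|---|---|
| 50:50 (70, 71) | chi-squared | 0.524 | 0.530 | 0.50 |
| 50:50 (70, 71) | Fisher | 0.407 | 0.414 | 0.48 |
| 60:40 (85, 56) | chi-squared | 0.603 | 0.432 | 0.51 |
| 60:40 (85, 56) | Fisher | 0.515 | 0.293 | 0.51 |
| 67:33 (94, 47) | chi-squared | 0.653 | 0.401 | 0.53 |
| 67:33 (94, 47) | Fisher | 0.551 | 0.219 | 0.53 |

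For the first row: 0.524 × 0.470 + 0.530 × 0.476 = 0.50. If the trial's hypothesis is true and uniform, significance in one level only is about as likely as not.

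**4. Power of an interaction test.** Suppose the effect exists in one level only (15% v 5% there, 15% v 15% in the other), with a 50:50 split and 70.5 per arm per level. On the risk-difference scale the variance of the contrast is (0.1275 + 0.0475)/70.5 + (0.1275 + 0.1275)/70.5 = 0.0061, so SE = 0.078. Then 0.10/0.078 = 1.28, and power is about P(Z > 1.96 − 1.28) = 0.25. This limits what the fix can deliver.

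**The case against.** The strongest reply is that this is a condensed article. A full protocol exists, an analysis plan may exist, and a testing hierarchy or exploratory label may sit in either. The article separates one primary outcome from the secondary ones, ties the two-sided 0.05 and the power to AL alone, and never says that a secondary p < 0.05 would establish benefit if AL is null. The subgroup factors are prespecified, and an interaction test is not excluded. Reporting unadjusted secondary results as supportive is common and defensible.

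Much of this stands. The primary error rate is not at risk, and the absence of a multiplicity section would not by itself be a finding. What does not fall away is the sentence itself: it applies one verdict to all variables directly after the per-stratum analyses, and a more careful analysis plan would have to contradict it.

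A reader might go further and infer that a false positive claim is more likely than not. The documents do not secure that:

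- The 66% needs 21 independent tests with no true difference anywhere. Testing at each visit is inferred from the two-group tests listed, and the figure falls below one half at a visit correlation of about 0.7 or more.
- Applying every secondary outcome and visit to every stratum gives 0.77 to 0.98, but the article does not say which outcomes are analysed by stratum.
- The Background cites a meta-analysis with less urinary, defecatory and sexual dysfunction after low ligation. If only quality of life and DFS are truly null, that full scope gives 0.41 to 0.62.
- For AL in four crossed cells, the nominal 1 − 0.95^4 = 18.5% drops to about 6% with Fisher's exact test at 39 per arm per cell and 10% AL in both arms (exact size 0.016 per cell; 1 − 0.984^4 = 0.06).
- The per-protocol repeat adds little, because the article expects the two analysis sets to agree closely.

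**Conclusion.** The point holds in limited form. The significance rule does not distinguish the single confirmatory test from secondary and subgroup results. The AL test keeps its 5% error. Where there are no true differences, the chance of at least one false positive among the secondary results is well above 5%: about 23% on the sparest count and about 0.4 to 0.66 with visit-wise testing. Both depend on the assumed number of tests, and the second also on the correlation between visits.

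The subgroup part does not depend on a null hypothesis. With the planned effect uniform across a factor, exactly one level reaches p < 0.05 in 48% to 53% of trials for splits from 50:50 to 67:33. Significance in one stratum only is therefore not evidence that the effect differs. This deserves correction, but it does not threaten the primary conclusion.

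**What to change.** Replace the significance sentence with wording to this effect:

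- Only AL in the intention-to-treat set is tested confirmatorily, at two-sided 0.05.
- Secondary outcomes are reported as estimates with 95% confidence intervals and labelled exploratory.
- For sex and for preoperative chemoradiotherapy, the treatment-by-factor interaction is reported with the estimate and confidence interval in each level. No significance claim is made within a stratum.

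The sample size, the data collected and the conduct of the trial do not change. The article reports that enrolment is still under way and provides an amendment route.

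There are two costs. A nominal p < 0.05 on a secondary or stratum result can no longer be claimed as significant. The interaction tests will also have low power (about 25% in the example above, even when the whole effect lies in one level), so a non-significant interaction must not be read as showing that the effect is uniform.
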